## Abstract

**Background:**

Postextraction ridge resorption compromises the aesthetics and function of the subsequent implant therapy or prosthetic rehabilitation. Several techniques are employed to reduce ridge resorption, ranging from basic socket fillers such as blood clot preservation to more advanced techniques using barrier membranes and bone grafts such as autografts, allografts, xenografts, and synthetic materials.

**Objective:**

The aim of this study is to evaluate and compare the effectiveness of alveolar socket preservation by using demineralized freeze-dried bone allograft (DFDBA) with titanium platelet-rich fibrin (T-PRF) and autologous dentin graft (ADG) with T-PRF. This assessment will be performed through comprehensive clinical, radiographic, and histomorphometric analyses. The primary objective of this study is to histologically evaluate the new bone formation in the extraction sockets preserved using either DFDBA with T-PRF or ADG with T-PRF. The secondary objective is to evaluate the dimensional changes, including ridge width and height at these healing points, as measured by clinical and radiographic methods. We will evaluate and compare the clinical, radiographic, and histomorphometric outcomes of using DFDBA with T-PRF versus ADG with T-PRF for maintaining socket integrity after tooth extraction. We will also ascertain which grafting technique facilitates the production of new bone during the healing phase and preserves alveolar ridge dimensions.

**Methods:**

This randomized controlled trial will involve 16 patients aged 22-60 years requiring tooth extractions and subsequent implant placement. Participants will be randomly assigned to one of the 2 groups: (1) socket preservation using DFDBA in combination with T-PRF or (2) socket preservation using ADG with T-PRF. At baseline, all the clinical variables will be assessed using UNC-15 probe and cone beam computed tomography radiographs. Extraction will be done atraumatically with minimal flap reflection by using periotomes. Postextraction sockets will be preserved using DFDBA+T-PRF or ADG+T-PRF. At 4 months, clinical and radiographic evaluations will be done, and the implant will be placed using a 2-stage protocol. Histomorphometric analysis will be performed after receiving bone samples during implant placement. At 3 months after implant placement, the second-stage surgery will be done.

**Results:**

Participant enrollment commenced in March 2024, and the study is scheduled to conclude postassessments and analyses by the end of 2025. The results of this study are anticipated to be accessible in late 2025. This study is not funded, and the results are expected to be published by 2026.

**Conclusions:**

This study represents valuable insights into the clinical effectiveness of 2 biologically driven socket preservation techniques. We hypothesize that the use of ADG combined with T-PRF will show similar or more effective outcomes in alveolar socket preservation demonstrated by enhanced bone formation and better maintenance of socket dimensions compared to DFDBA combined with T-PRF without increased morbidity.

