#### Adverse Event Reporting and Harms

Data will be collected, assessed, and spontaneously reported during adverse events and other unintended effects of trial interventions or trial conduct.

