### Statistical Analysis

Mean (SD) values will be found for each clinical periodontal parameter such as plaque index, papillary bleeding index, probing pocket depth, width of keratinized gingiva, clinical attachment level, and marginal bone level. Next, from baseline to 4 months, the mean data will be statistically analyzed. To equate baseline to 4-month findings for every patient, Student paired *t* test will be employed for intragroup data comparison, while the Student unpaired 2-sided *t* test will be utilized for intergroup comparison. If the *P* value exceeds .05, the observed difference will be considered nonsignificant; if it remains below .05, it will be considered significant.

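### The hypothesis that ADG is similar or better than DFDBA cannot be supported in its similar part: the only between-group inference is a difference test at P<.05 with 8 patients per arm

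*Protocol article*

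**What the plan says.** The protocol article states its hypothesis in the abstract's Conclusions: the ADG arm "will show similar or more effective outcomes in alveolar socket preservation", judged against the DFDBA arm. The same sentence goes on to predict more bone and better-kept socket dimensions, and it ends with a harms clause, "without increased morbidity". It thus mixes a not-worse claim, a superiority claim and a harms claim.

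Statistical Analysis gives the between-group method: "the Student unpaired 2-sided *t* test will be utilized for intergroup comparison". The decision rule is "If the *P* value exceeds .05, the observed difference will be considered nonsignificant; if it remains below .05, it will be considered significant". The article gives no non-inferiority or equivalence margin and no rule for concluding similarity.

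Sample Size Calculation uses α=.01, β=.01, means of 0.72 (spontaneous healing) and 1.33 (ADG) and SDs of 0.23 and 0.24, and arrives at 8 per group. Under Randomization and Masking, the control arm is DFDBA with T-PRF.

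On harms, Adverse Event Reporting and Harms says: "Data will be collected, assessed, and spontaneously reported during adverse events". Neither the primary nor the secondary outcomes include morbidity.

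**The concern.** Being similar to or better than an active control is a claim that the new treatment is not worse. It needs a stated amount by which ADG may fall short and a confidence limit to compare with that amount. A difference test supplies neither. P<.05 in favour of ADG supports the superiority part, but no result of the stated test supports similarity.

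The article offers no other route to the similar part, so a nonsignificant P value is the result most likely to be put forward for it. Read that way, the hypothesis would survive every outcome except a significant deficit for ADG, and 8 per arm often misses even a large one. What is at stake is whether the trial's main conclusion could say that two grafts perform alike when the data do not exclude a substantial difference.

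**Working it through.** **1. The plan's own sample size.**
- Pooled SD = √((0.23² + 0.24²)/2) = √0.05525 = 0.235.
- Difference = 1.33 − 0.72 = 0.61.
- Two-sided α=.01, β=.01: n per group = 2 × [0.235 × (2.576 + 2.326)/0.61]² = 7.14, rounded up to 8.

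The stated 8 per group reproduces. It is a calculation for detecting a difference and contains no margin.

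**2. Precision with 8 per arm.** All steps from here assume 8 analysed patients per arm. The standard error of the difference is SD × √(2/8) = 0.5 SD, with 14 degrees of freedom and t(.975) = 2.145.
- 95% CI half-width = 2.145 × 0.5 SD = 1.07 SD.
- With the planning SD this is 1.072 × 0.235 = 0.25, and 0.25/0.61 = 41% of the planning difference. These absolute figures are illustrative only, because the inputs come from ADG versus spontaneous healing and not from the contrast studied here.

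**3. How often a real ADG deficit gives P>.05.** Noncentral t, 14 df, noncentrality = deficit in SD/0.5, two-sided .05:

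| True ADG deficit | Power | Probability of P>.05 |
|---|---|---|
| 0.5 SD | 15% | 85% |
| 0.8 SD | 32% | 68% |
| 1.0 SD | 46% | 54% |

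**4. What 8 per arm could show about non-inferiority.** One-sided .025, true difference zero, noncentrality = margin in SD/0.5:

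| Margin | Power with 8 per arm |
|---|---|
| 1.0 SD | 46% |
| 1.07 SD | about 51% |
| 1.51 SD | 80% |

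A margin equal to the CI half-width is therefore met only about half the time, even when the arms are truly identical.

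**5. Size needed for narrower margins.** The article names no margin, so these are assumed fractions of 0.61, with SD 0.235, 80% power, one-sided .025 and the normal approximation. They carry the same caveat about the planning inputs.

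| Assumed margin | n per group |
|---|---|
| 10% (0.061) | 234 |
| 20% (0.122) | 59 |
| 25% (0.153) | 38 |
| 33% (0.203) | 21 |
| 50% (0.305) | 10 |

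Every margin in this range needs more than 8 per group.

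**6. Morbidity.** With zero events in 8 patients, the one-sided 95% upper limit for the true rate is 1 − 0.05^(1/8) = 31%. This applies to any arm of 8, but it shows that an absence of increased morbidity cannot be established here.

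**The case against.** A reader might infer that the plan intends to report P>.05 as similarity. It does not say so. Statistical Analysis says only that "the observed difference will be considered nonsignificant", which is a correct description. The plan leaves the misreading open but does not prescribe it.

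A reader might also infer that this is a non-inferiority trial without its machinery. The documents do not support that. The hypothesis sentence goes on to superiority wording. The aims in the abstract's Objective, in Study Design and at the end of the Discussion are comparative, and a two-sided t test and a difference-based sample size fit those aims. The conflict lies between part of one abstract sentence and the rest of the design.

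On harms, adverse events are to be collected, assessed and reported, and they need not be listed as efficacy outcomes. How they are tabulated can be left to a fuller document. What remains is that "without increased morbidity" is too strong as a hypothesis for arms of 8.

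A fuller protocol or analysis plan could add a margin. But the hypothesis, the test and the sample size are all fixed in this article, and a later margin would reach 80% power with 8 per arm only if it were about 1.5 SD wide or more.

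**Conclusion.** Wrong as written, and it should be fixed. The similar part of the hypothesis has no valid test in this plan; the superiority part does. No stated procedure would give a wrong number. The error is in what the trial would be entitled to conclude, so it falls short of a fault that invalidates the design.

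The size rests on the figures in SD units (CI half-width 1.07 SD, 54% nonsignificant at a 1 SD deficit, 1.51 SD margin for 80% power). These depend only on 8 analysed patients per arm, a common SD and roughly normal data, and not on the planning means. Any loss of patients would make them worse.

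**What to change.** - Restate the hypothesis as a two-sided superiority or estimation question, in line with the comparative aims in the abstract's Objective.
- Report the mean between-group difference in percentage new bone with its 95% CI, and base conclusions on that interval.
- Add to Statistical Analysis that P≥.05 will not be interpreted as similarity or equivalence.
- Keep the claim of similarity only if a margin is justified in advance and judged by the confidence limit. Acknowledge then that, with a true difference of zero, 8 per arm has 80% power only for a margin of about 1.5 SD, and about 50% for a margin of about 1.07 SD.
- Drop the no-increased-morbidity clause as a hypothesis and present adverse events by arm descriptively.

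The cost is a change of wording and a more modest claim, with no extra patients or measurements. Keeping similarity with a narrower margin would instead require a larger trial. The change should be made before the between-group results are seen.

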**Trial Registration:**

Clinical Trials Registry – India CTRI/2024/05/068192; https://ctri.nic.in/Clinicaltrials/pmaindet2.php?EncHid=MTI1NzIz&Enc=&userName=

**International Registered Report Identifier (IRRID):**

DERR1-10.2196/70649

## Introduction

Dental implants are the most widely used and reliable treatment method for individuals with fully or partially edentulous arches. The time frame for implant insertion following extraction is currently the main concern of implant therapy rather than osseointegration. Alveolar socket preservation following tooth extraction is one of the most important dental advanced skills, as numerous conditions such as traumatic extraction techniques, periodontal diseases, tumors, infections, or cysts can cause the loss of alveolar bone [1]. Alveolar ridge resorption is one of the physiological alterations that takes place following tooth extraction. After tooth extraction, alveolar ridge modeling peaks over the first 4-6 weeks, as is well known, while progressive atrophy may persist over time at a slower rate [2]. Ridge atrophy results from a substantial degree of physiologic remodeling that occurs in the alveolar socket following tooth extraction [3]. To minimize stress to the alveolus and accomplish minimal socket enlargement, atraumatic extraction must be performed. Treatment options for ridge atrophy include several forms of bone and/or soft tissue augmentation; nevertheless, these methods are known to have varying degrees of success and predictability. It is believed that socket grafting, which requires the use of grafting materials with or without barrier membranes, reduces the amount of dimensional shrinkage that occurs in the alveolar socket following tooth extraction.

For the best results, an ideal bone graft should have osteoconduction, osteoinduction, and osteoproliferation properties [4]. A range of surgical methods and biomaterials have been created to enable socket preservation. For this objective, several bone grafting methods, including synthetic and natural graft materials, have been tried. The most often used, clinically approved, or modified bone allograft material for periodontal repair is demineralized freeze-dried bone allografts (DFDBA). Bone morphogenetic proteins (BMPs) are linked to the osteoinductive capacity of DFDBA; this particular BMP combination includes BMPs 2, 4, and 7. DFDBA breaks down at a faster rate, which promotes the growth of new bone [5]. Its primary application is in the reconstruction of osseous deformities.

Growth factors such as platelet-derived growth factor are present intracellularly and essential for the healing of wounds. Utilizing platelet concentrates has several benefits. They are crucial to regeneration. Their application has been effectively linked to bone and connective tissue repair. Platelet concentrates promote bioactivity and demonstrate nonstimulative properties. Titanium platelet-rich fibrin (T-PRF) is one of the third-generation platelet concentrates [6]. This platelet concentrate is recognized to remove the potentially harmful effect of silica, which is found in glass vacuum containers used to prepare PRF. Platelet and leukocyte cell–enriched fibrin or T-PRF is made with titanium and resembles fibrin made with the traditional PRF process. Titanium is the most corrosion-resistant metal with the highest amount of toughness. Furthermore, titanium has an amazing osseointegration quality [6]. T-PRF presents a longer resorption time and a denser fibrin structure compared to PRF, making it a promising option for the sustained release of growth factors [7].

Histologically stated, hydroxyapatite makes up the majority of the inorganic structure that makes up human enamel and dentin, which is composed of 45% organic material. Type I collagen and BMP comprise most of the organic components. An autologous dentin graft (ADG) is a viable substitute for alveolar socket preservation due to its composition of organic and inorganic components as well as its ability to promote bone formation and support bone growth [4-6]. The osteoconductive characteristics of human dentin are attributed to 4 types of calcium phosphate: amorphous calcium phosphate, tricalcium phosphate, octacalcium phosphate, and hydroxyapatite. As hydroxyapatite in dentin is primarily found as calcium phosphate with a low crystal concentration, osteoclast activity can readily break it down. Approximately 90% of its 20% organic content is composed of type I collagen network; the remaining 10% is made up of noncollagenous proteins (such as phosphoprotein, sialoprotein, osteocalcin, and osteonectin, which help calcify bone), and 10% is made up of growth factors (like insulin-like growth factor and BMPs, which give teeth their osteoinductive properties) [8]. Owing to all these properties, it can be considered as potential graft material and has been used in the past for regenerative procedures.

Accurate assessments need the establishment of a consistent point for cone beam computed tomography (CBCT) linear measurements. CBCT is currently the most widely used 3D radiographic imaging technique in dentistry, offering several benefits over traditional CT scans and 2D imaging instruments. A more precise method involves using subtraction analysis of CBCT data [9]. The fundamental advantage of using CBCT in implant dentistry is its ability to provide detailed volumetric imaging data of the craniofacial region for preoperative and diagnostic planning.

CBCT radiographs have been reported to sometimes show certain discrepancies; hence, to eliminate those in the results, the outcomes will be confirmed by histomorphometric analysis. The bone sample for the histomorphometric analysis will be obtained using trephine bur during implant placement [10,11].

Hence, in this investigation, the aim is to clinically, radiographically, and histomorphometrically evaluate the effectiveness of DFDBA with T-PRF and that of ADG with T-PRF for socket preservation.

## Methods

### Study Design

This research is a clinical trial with randomized controlled prospective parallel arms to achieve a side-by-side comparison between ADG with T-PRF and a commercially available DFDBA bone graft with T-PRF.

### Ethical Considerations

This study was approved by the Institutional Ethics Committee of Datta Meghe Institute of Higher Education and Research, Wardha, Maharashtra, India (DMIHER(DU)/IEC/2024/226). All participants were informed about the study objectives, procedures, potential risks, and benefits prior to enrollment. Participation in this study was completely voluntary, and individuals were free to withdraw or opt out at any time without providing a reason and without any effect on their ongoing or future dental care at the institution. All data collected from participants were anonymized prior to analysis. Personal identifiers (name, address, phone number, and registration details) were removed and replaced by coded ID numbers. Access to the linking file was restricted to the principal investigator and stored on a password-protected institutional server to ensure confidentiality and data security. Participants did not receive any monetary compensation for taking part in the study. However, all clinical procedures performed as part of the research protocol were provided free of cost, ensuring no financial burden on participants. As no payment was made in foreign currency, no USD exchange rate was applicable. Written informed consent was obtained from all participants prior to their inclusion in the study, in accordance with the Declaration of Helsinki and institutional ethical guidelines.

### Study Population

Based on the necessity for a single tooth replacement via implant fixture, 16 healthy individuals without a history of any systemic disease will be enrolled in this research from the Department of Periodontics, Sharad Pawar Dental College, Sawangi (Meghe), Wardha. The participants will be informed about the study’s goal, methodology, and design prior to the study start. Written consent will be taken.

### Oversight and Monitoring

#### Composition of the Coordinating Center and Trial Steering Committee

The committee consists of the following: the head of the department of periodontics, postgraduate guide, research scientist, principal investigator, surgeon, statistician, data manager.

#### Composition of the Data Monitoring Committee

The data monitoring committee consisted of the research in-charge of the institute and research in-charge of the department.

#### Adverse Event Reporting and Harms

Data will be collected, assessed, and spontaneously reported during adverse events and other unintended effects of trial interventions or trial conduct.

#### Frequency and Plans for Auditing Trial Conduct

The project management group meet will review the trial conducted every month. The trial steering group and the independent data monitoring and ethics committee meet will review and conduct the trial period till the trial is complete.

### Eligibility Criteria and Recruitment

Following the clinical and radiographic assessments, 16 patients must precisely meet the criteria that are listed below.

#### Inclusion Criteria

The inclusion criteria are as follows.

Patients indicated for implant following tooth extraction for reasons such as residual roots, overretained primary teeth, nonrestorable carious lesions, internal and external resorption, fractured roots, and failed endodontic therapyPatients with a complete mouth plaque score of less than 25%, indicating good oral hygienePatients with a natural tooth in oppositionPatients with adjacent teethPatients with a thick gingival biotypePatients with a 4-mm bone apical to the root apexPatients with bone quality of D-1, D-2, or D-3 type

#### Exclusion Criteria

The exclusion criteria are as follows.

Individuals with systemic conditions such as diabetes mellitus, osteoporosis, blood-related diseases, and titanium allergy that could compromise their overall health and impede the process of bone healing and repairIndividuals with a space between the maxilla and mandibleIndividuals with parafunctional habits like clenching or bruxismIndividuals with a history of substance misuse, excessive smoking, or drinkingIndividuals with D-4 bone qualityIndividuals who have undergone chemotherapy and radiationIndividuals with temporomandibular joint disordersIndividuals with untreated oral health conditionsPregnant and lactating mothers

### Recruitment

Figure 1 presents a simplified diagram that outlines the study protocol based on the CONSORT (Consolidated Standards of Reporting Trials) guidelines (Multimedia Appendix 1).

**Figure 1 figure1:**
[figure not shown]
A simplified diagram that outlines the study protocol based on CONSORT (Consolidated Standards of Reporting Trials). ADG: autologous dentin graft; DFDBA: demineralized freeze-dried bone allograft; T-PRF: titanium platelet-rich fibrin.

### Primary Outcomes

Four months following the socket preservation procedure, the formation of new bone and changes in the alveolar socket dimensions in both groups will be assessed by radiological and histomorphometric analyses. Histomorphometric evaluations will be performed on bone core biopsies obtained at the time of implant placement at 4 months after the extraction. These samples will be processed using standard histological techniques, stained with hematoxylin and eosin, and assessed under light microscopy. Quantitative measurements such as the percentage of new bone formation, number of osteocytes, and trabecular patterns will be analyzed using Planmeca Romexis software (version 6.2.0; Planmeca Oy) to determine the measurement of bone dimensions, apico-coronal ridge height, and density in Hounsfield units.

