### Secondary Outcomes

After 4 months of the surgical procedure, linear phenotypic dimensional changes in the thickness of soft tissues and the midfacial and midpalatal bones at baseline and at 4 months after healing at 2 locations will be evaluated.

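### Socket dimensions are secondary in the objectives but primary in the outcomes section, and no section says which result decides the trial

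*Protocol article*

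**What the plan says.** In the Protocol article's abstract, the Objective ranks the two aims: "The primary objective of this study is to histologically evaluate the new bone formation in the extraction sockets", and then "The secondary objective is to evaluate the dimensional changes, including ridge width and height at these healing points".

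Under Methods, the Primary Outcomes section puts both under one heading: at four months, "the formation of new bone and changes in the alveolar socket dimensions in both groups will be assessed by radiological and histomorphometric analyses". It then lists "Quantitative measurements such as the percentage of new bone formation, number of osteocytes, and trabecular patterns", to be analysed with CBCT software "to determine the measurement of bone dimensions, apico-coronal ridge height, and density in Hounsfield units".

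The Secondary Outcomes section covers a different set, namely "linear phenotypic dimensional changes in the thickness of soft tissues and the midfacial and midpalatal bones". Ridge width and height do not appear there.

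The Sample Size Calculation uses means and SDs of newly formed bone with alpha .01 and beta .01, and ends by calling the size adequate for pocket depth, which is in neither outcome section. The Statistical Analysis section names plaque and bleeding indices, probing depth, keratinized gingiva, attachment level and marginal bone level. Its rule for a P value is "if it remains below .05, it will be considered significant".

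**The concern.** A reader cannot tell from the article whether a change in socket dimensions is part of the primary result. Suppose the four-month cores show no difference in new bone but CBCT ridge height differs between arms. Under the Objective, the primary comparison has failed and the ridge finding is secondary. Under the Primary Outcomes section, the same data allow a positive primary finding. With 8 patients per arm, the two kinds of measurement may well disagree.

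The other sections do not settle the matter. The hypothesis in the abstract's Conclusions refers to both bone formation and socket dimensions. The sample-size section brings in a third candidate, pocket depth. The analysis section names neither new bone nor ridge dimensions.

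**Working it through.** **1. The sections side by side**

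| Section | New bone (histology) | Ridge or socket dimensions | Other |
|---|---|---|---|
| Abstract, Objective | Primary | Secondary | – |
| Primary Outcomes | Primary | Primary, including ridge height | Osteocyte number, trabecular pattern, density |
| Secondary Outcomes | – | Ridge width and height not listed | Soft-tissue, midfacial and midpalatal bone thickness |
| Sample Size Calculation | Basis of the calculation, alpha .01 | – | Pocket depth, in the closing sentence |
| Statistical Analysis | Not named | Not named | Clinical periodontal parameters, .05 |
| Discussion | Histomorphometry is the main focus | – | – |

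The first two rows contradict each other on socket dimensions.

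**2. Which variable the size was built on**

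Inputs (Sample Size Calculation): SDs 0.23 and 0.24, means 0.72 and 1.33, 1:1 allocation, alpha .01, beta .01.

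n per group = (z for alpha + z for power)² × (SD1² + SD2²) / (difference)²

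- SD1² + SD2² = 0.0529 + 0.0576 = 0.1105
- Difference = 1.33 − 0.72 = 0.61; squared, 0.3721
- Two-sided alpha .01, power .99: (2.576 + 2.326)² = 24.03
- n = 24.03 × 0.1105 / 0.3721 = 7.14, rounded up to 8

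The stated 8 per group is reproduced from the newly-formed-bone inputs alone. These inputs compare ADG with spontaneous healing and carry no unit, so the check shows which variable the size was based on. It says nothing about power for the comparison this trial makes.

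**3. Error rate if any one primary outcome could declare success**

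The article does not state this rule; it is assumed here to size the risk. The number of primary outcomes k is also uncertain: two if new bone and dimensions are the outcomes, six if each named measure counts (three histological, three radiographic). For independent tests at .05:

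- k = 2: 1 − 0.95² = 9.75%
- k = 6: 1 − 0.95⁶ = 26.5%

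Measures taken from one socket are unlikely to be independent. A simulation under no treatment difference (8 per group, two-sided unpaired t tests, 40,000 trials per setting, assumed equal correlation) gave:

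| Assumed correlation | k = 2 | k = 6 |
|---|---|---|
| 0.3 | 9.4% | 24.6% |
| 0.5 | 9.0% | 21.6% |
| 0.8 | 8.1% | 14.3% |

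**4. Other rules give other answers**

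- If both of two outcomes had to reach .05, the rate with no difference on either would be 0.8% at correlation 0.5. The cost would be power.
- If the planning alpha of .01 were the test level, an any-win rule with independent outcomes would give 1 − 0.99² = 2.0% for two and 1 − 0.99⁶ = 5.9% for six.

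**The case against.** The strongest reply is that the article leans clearly one way. The Objective, the sample-size inputs and the Discussion all point to histological new bone, and the Results section says the main paper will report on the primary objective. On this view the Primary Outcomes section is the outlier. That stands, and it is why the repair is easy. It does not remove the contradiction: the section whose job is to define the primary outcome is the one that disagrees.

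A reader might infer that the trial's false-positive rate is 26%. The documents do not support this as a fact. The .05 rule follows a list of clinical periodontal parameters, so applying it to these outcomes is an inference, though it is the only test threshold given. No any-win rule is stated. A multiplicity procedure may sit in an analysis plan that is not shown, and its absence from an article is not a fault. The sentence listing the measures is also unclear: osteocyte number, trabecular pattern and density can be read as components of two outcomes, and bone dimensions overlap with ridge height.

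A reader might also infer that clinical probe readings of the ridge are unmasked, or that clinical and CBCT readings compete as the deciding measure. The article says neither. It is silent on the clinical examiner's masking, and its Primary Outcomes section refers only to radiological and histomorphometric assessment.

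**Conclusion.** The concern holds as an internal contradiction. Ridge dimensions are secondary in the Objective, primary in Primary Outcomes and absent from Secondary Outcomes, and no section says which result decides success. The sample-size and analysis sections add to the conflict through alpha .01 against .05 and through the pocket-depth sentence.

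The contradiction rests on the text alone and needs no assumption. The error rates in the working are conditional on success by any one primary outcome at .05, on a count between two and six, and on correlation between 0 and 0.8. Within those limits every figure exceeds 5%. The article does not show that the trial will be analysed this way.

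**What to change.** - **Primary Outcomes:** name one primary outcome, the percentage of newly formed bone in the 4-month core. This agrees with the Objective, the variable used for the sample size and the Discussion.
- **Secondary Outcomes:** add ridge width and height. Treat osteocyte number, trabecular pattern and density as secondary or supportive.
- **Statistical Analysis:** name the primary variable and state one alpha for it, .01 or .05, that agrees with the Sample Size Calculation.
- **Sample Size Calculation:** remove the pocket-depth sentence or reconcile it with the calculation on newly formed bone.

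If the investigators do want new bone and dimensions both to be primary, the alternative is to say so in the Objective as well and to state how the two combine.

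The recommended change is to wording only. It alters no procedure, visit or patient number. Its price is that dimensional results can no longer be presented as primary. Because enrolment has begun, the change should be dated and made before outcome data are analysed by arm.
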